#### Difference in mean costs

Costs of services used by each participant will be estimated from the quantities of each type of resource used, multiplied by the unit cost. A total cost per case per patient will be calculated based on all of the above which in turn will allow for an average cost per case per trial arm for treatment and the control group, presented with rates of significance of difference between arms.

A cost utility analysis will be performed combining the cost data with the primary clinical outcome measures for functional disability (BSDI©) and disease severity (JRS). A further cost utility analysis will be performed on quality of life (CDQ-24), a secondary clinical outcome measure for the trial.

Cost per unit of therapeutic change, whether this be clinical improvement, reduced disability, change in quality of life or increased patient satisfaction will be calculated.

As part of the economic evaluation, non-parametric bootstrapping will be used to develop confidence intervals around the incremental cost-effectiveness ratio based on costs and associated effectiveness data (functional disability, disease severity, quality of life and patient satisfaction). This process also generates acceptability curves to illustrate the uncertainty associated with the estimate of costs and effects combined and (probabilistic) estimates of affordability given potentially different decision-maker cost thresholds.

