Studies of patient-initiated services, where the patient rather than healthcare professional initiates treatment and care, have shown promise. These services provide patients with information on when and how to access services, rather than having regular time-based scheduled appointments. A systematic review conducted by Whear et al. [8] synthesised the evidence for this model of care across three conditions: irritable bowel disease, breast cancer and rheumatoid arthritis. Overall, there were few differences in psychological or health-related quality of life outcomes between those initiating their own outpatient follow-up appointments compared to standard care, despite in many cases patients having less contact with healthcare professionals. Patient and clinician satisfaction were significantly greater in the patient-initiated services compared to regular appointment scheduling. Another more recent trial has also found significant reductions in healthcare utilisation without compromising clinical or psychosocial well-being [9].

Adopting a patient-led model of care has the potential to reduce morbidity and disability in patients with a short-term response to botulinum toxin. Conversely, this may also reduce unnecessary hospital visits and treatment for patients with a longer-term response. There is currently one patient-initiated, nurse-led botulinum toxin clinic running in the UK for patients with blepharospasm or hemifacial spasm [10], but is yet to be evaluated in comparison to usual care. Due to the variable nature of the duration of response to treatment, blepharospasm and hemifacial spasm are appropriate conditions in which to evaluate a service of this nature. This study, therefore, provides a unique opportunity to empower patients with dystonia to take control of their treatment scheduling and optimise the effects of botulinum toxin, by allowing them to seek treatment when they feel it is necessary rather than it being dictated by the clinical team.

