## Methods

### Study design

This study will be mixed methods adopting a concurrent embedded strategy [11], whereby a qualitative study will be embedded within a larger single-masked RCT, with the RCT as the dominant component. This design will provide information on effectiveness and also an in-depth assessment of the patient experience. The RCT will be a parallel-group, explanatory, superiority RCT designed to assess the effectiveness of a patient-initiated botulinum toxin service compared to usual care. Semi-structured interviews will be conducted with a sample of intervention participants in order to assess acceptability of the service.

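### The bootstrap interval on the cost-effectiveness ratio is planned without a condition and cannot be read if replicates straddle zero effect; net benefit from the same replicates would avoid this

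*Protocol article*

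**What the plan says.** The section Difference in mean costs of the protocol article plans that "non-parametric bootstrapping will be used to develop confidence intervals around the incremental cost-effectiveness ratio". The ratio is to be based on costs and "associated effectiveness data (functional disability, disease severity, quality of life and patient satisfaction"), that is, on the BSDI, JRS, CDQ-24 and CSQ. The next sentence adds: "This process also generates acceptability curves to illustrate the uncertainty associated with the estimate of costs and effects combined", and mentions varying decision-maker thresholds without giving values. Net benefit is not named. Nothing is said about an effect difference close to zero.

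Three other statements bear on how large the effect may be:

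- Study design calls the trial a "parallel-group, explanatory, superiority RCT", and Table 2 under Sample size uses d = 0.25 to 0.40.
- Background reports of earlier patient-initiated services that "there were few differences in psychological or health-related quality of life outcomes between those initiating their own outpatient follow-up appointments compared to standard care", and of a later trial that it found "significant reductions in healthcare utilisation without compromising clinical or psychosocial well-being".
- Background also says: "Patient and clinician satisfaction were significantly greater in the patient-initiated services compared to regular appointment scheduling".

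**The concern.** The ratio of cost difference to effect difference has no value at zero effect and jumps from one extreme to the other on either side of it. Its sign is also ambiguous. On standardised scales, a saving of 0.2 with a gain of 0.1 gives -0.2/0.1 = -2, and an extra cost of 0.2 with a loss of 0.1 gives 0.2/(-0.1) = -2. The first service is better and cheaper, the second worse and dearer, and the ratio does not tell them apart. Once replicates lie on both sides of zero effect, ordering them by the ratio no longer orders them from good to bad.

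The direction of the cost difference is open too. Background foresees fewer visits for patients with a long response and less morbidity for those with a short one, and Intervention sets no upper limit on patient-initiated appointments. Replicates could therefore fall in all four quadrants. At stake is the interval that shows readers how uncertain the economic result is, for each of four effect measures.

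**Working it through.** **Inputs.** Recruitment target 266 (Abstract), 1:1 allocation (Randomisation), completion 79%, ICC 0.3, four time points and d = 0.25 to 0.40 (Sample size and Table 2). Completers: 266 × 0.79 = 210, or 105 per arm. The article gives no cost data.

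**1. The plan's own figures.** For a comparison of means over four time points, SE = √[(2/n) × (1 + 3 × 0.3)/4] = √[(2/n) × 0.475], and power = Φ(d/SE − 1.96).

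| d | n per arm (Table 2) | SE | Power recomputed | Power stated |
|---|---|---|---|---|
| 0.25 | 115 | 0.0909 | 0.785 | 0.80 |
| 0.30 | 80 | 0.1090 | 0.786 | 0.80 |
| 0.35 | 59 | 0.1269 | 0.788 | 0.80 |
| 0.40 | 46 | 0.1437 | 0.795 | 0.81 |

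The formula agrees with Table 2 to within 2 percentage points, so it is a fair basis for the next step.

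**2. How often the effect interval includes zero.** The article does not say which effect estimate enters the ratio, so two cases bound the range:

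- single follow-up: SE = √(2/105) = 0.138;
- mean of four time points, ICC 0.3: SE = 0.138 × √0.475 = 0.095. This is the favourable case, since the section Changes over time codes only three time points.

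P(95% interval includes 0) = Φ(1.96 − d/SE) − Φ(−1.96 − d/SE). For d = 0.25, single follow-up: d/SE = 1.811, giving Φ(0.149) − Φ(−3.771) = 0.56.

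| True d | Single follow-up | Mean of four time points |
|---|---|---|
| 0 | 0.95 | 0.95 |
| 0.10 | 0.89 | 0.82 |
| 0.25 | 0.56 | 0.25 |
| 0.30 | 0.42 | 0.12 |
| 0.35 | 0.28 | 0.04 |
| 0.40 | 0.17 | 0.01 |

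**3. What this does to the interval.** A simulation used 1,000 trials, 2,000 bootstrap replicates each and 105 patients per arm. All of the following are assumptions: effect SD 1, exponential costs with SD 1, true cost difference +0.2 or −0.2 SD, no correlation of cost and effect, threshold 1, percentile intervals. Ranges are over the two cost differences.

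| True d | Trials with over 2.5% of replicates on each side of zero effect | Median width, ratio interval | Median width, net-benefit interval |
|---|---|---|---|
| 0 | 94% | about 32 | 0.75–0.76 |
| 0.10 | 88% | 27–29 | 0.75 |
| 0.25 | 53–56% | 7–8 | 0.75–0.76 |
| 0.40 | 16–18% | 2.1–2.3 | 0.76 |

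The same ratio sign arose from opposite quadrants (each above 1% of replicates) in about 74%, 70%, 49–53% and 18–22% of trials, in the order of the rows. Coverage of the ratio interval was 96–98% where the true ratio exists (d above 0), and of the net-benefit interval 94–96%. The fault is therefore width and loss of meaning, not undercoverage.

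**4. Why net benefit is stable.** Net benefit is threshold × effect difference − cost difference. It has no denominator. At threshold 1 the two cases under the concern, both with ratio −2, give 0.1 + 0.2 = 0.3 and −0.1 − 0.2 = −0.3.

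**The case against.** The strongest reply is that much of the remedy is already planned. At each threshold an acceptability curve is the share of replicates with positive net benefit, so it is defined in every quadrant. That stands and shrinks the point. What the curve does not give is the size of net benefit or an interval for it, and it does not stop an unreadable ratio interval being reported beside it.

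Second, the article does not say that percentiles of the ratio will be taken, and such detail may belong in an analysis plan that is not shown. It is fair that the percentile method in the simulation is an assumption. But the target of the interval, the ratio, is fixed in the text, and the difficulty at zero effect lies in the ratio, not in the type of bootstrap interval.

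Third, a reader might infer from Background that a near-zero effect is the expected outcome, so that the interval will probably be useless. The documents do not support this. The trial is a superiority trial planned on d = 0.25 to 0.40. The same Background paragraph reports greater satisfaction with patient-initiated care, and satisfaction is one of the four effect measures. The review it cites concerns other conditions. A small effect is plausible for quality of life, no more. Nor may one infer that the interval would be wrong in the sense of missing the true value: simulated coverage was at or above nominal.

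Fourth, net benefit needs a value per point on each scale, and the article gives none. True, but the planned acceptability curves need the same values.

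**Conclusion.** The point holds in a limited form. The article commits to an interval on the ratio for four effect measures with no condition. That interval cannot be interpreted when the replicates straddle zero effect. The risk is material at the smallest planning effect (about 25% to 56% of trials), low at the largest (1% to 17%) and high at d = 0.10 (82% to 89%). These figures assume 105 completers per arm and a normal approximation. The lower end of each range also assumes the mean of four time points with ICC 0.3, the upper end a single follow-up. The interval widths rest on assumed costs and show the pattern only. This is a cheap improvement to a secondary analysis and does not touch the clinical comparison.

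**What to change.** Change the bootstrap text in Difference in mean costs to say:

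- incremental net benefit is reported from the same replicates, with a 95% interval, over the same threshold range as the acceptability curves;
- the cost-effectiveness plane is shown with it;
- an interval for the ratio is given only when the replicates lie essentially on one side of zero effect, and otherwise the point estimate alone. The cut-off for this is a convention and should be fixed in advance.

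The cost is a sentence or two and a little extra reporting, since no new resampling is needed. The one real demand is a stated threshold range per scale point for each of the four outcomes, which the planned curves require in any case.

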#### Acceptability of the service

The questionnaire used to capture participants’ views of acceptability of the intervention will be validated after data has been collected. Recognised and widely employed questionnaire validation methods will be used to assess for internal consistency, concurrent, discriminant and predictive validity.

### Qualitative analysis

The semi-structured interviews will be digitally recorded with the participant’s consent and transcribed verbatim by a professional transcribing company. Any information which could identify a participant will be anonymised. The data generated from these semi-structured interviews will be analysed using framework analysis [38]; a method for identifying, analysing and reporting patterns within data, using NVivo Software (Version 10) [39]. This method allows themes to be identified across a dataset and is appropriate for use in studies with a focused research question, as in the case of this study. Framework analysis involves searching across a data set to find the key issues and themes following five steps: (1) familiarising yourself with your data, (2) identifying a thematic framework, (3) indexing, (4) charting, and (5) mapping and interpretation [38].

In addition to this six-phase process, four validity criteria will be employed: (1) an audit trial which involves detailed quotes from the participant’s transcripts to provide evidence for the interpretation offered, (2) a peer panel: an auditor will be asked to go through randomly selected sections of transcripts to confirm the pattern of analysis, (3) the researchers will attempt to recognise their own values, interests and views and the role that they may play in their understanding of the transcripts. Doing this can help the reader to interpret the researcher’s data and analysis. A reflective diary will be kept by the researcher, where notes are kept about initial thoughts and feelings, the main points that arise in the interview and any factors that the researcher felt influenced the interviewee. These will be taken into account throughout the analysis process, and (4) an independent audit: an independent auditor familiar with framework analysis will be asked to check the validity of the ‘final report’.

## Research ethics approval

The trial has received full NHS Research Ethics Committee (REC) approval (REC reference: 15/LO/0439) from London – Queen Square REC. Patients must provide written informed consent to take part in the study. Any data collected from the study participants will be anonymised and no identifying information will be used in publications.

## Dissemination

The study results will be disseminated to relevant healthcare professionals via appropriate pre-identified healthcare journals. The results will also be disseminated to the public through the publicly available clinical trials database clinicaltrials.gov.uk. The results will also be presented at relevant scientific conferences.

## Patient and public involvement

Two patients with blepharospasm and hemifacial spasm have been invited to join the study management group. These patient members have provided valuable feedback on study materials (e.g. information sheets, consent forms) and acceptability of study measures and will help with interpretation and dissemination of the research findings. The trial will also be presented at a Blepharospasm Patient Study Day organised by MEH in November 2015 to gain feedback from patients about the acceptability of the intervention from their perspective.

## Discussion

Given the shift away from the paternalistic model of healthcare, it is important to provide patients with the tools to take a more active role in knowing and managing their health. This trial will enable patients with dystonia to control the timing of their appointments and ultimately manage their own symptoms. This study is the first RCT to assess the effectiveness of patient-initiated treatment model for patients with blepharospasm and hemifacial spasm, whilst improving patient satisfaction with care, in comparison to treatment as usual.

The evaluation of this new service will use a rigorous mixed-methods design to explore whether empowering patients to initiate their own appointments allows for a more stable pattern of disease severity and symptoms, whilst improving patient satisfaction and acceptability with their care, and quality of life. The costs of delivering the service, and the impact it has on other healthcare use will be measured and compared in relation to control participants. The authors do not anticipate any safety concerns for the trial; however, appropriate risk assessment and monitoring procedures have been implemented.

If the new model is shown to be effective in maintaining a more stable pattern of disease severity, symptoms and disability, and at the same time being satisfactory and acceptable to patients, whilst being cost-effective, this will have significant implications for service organisation across the NHS.

## Trial status

Patient recruitment for this trial began in August 2015.

## Abbreviations

A&E: accident and emergency
AE: adverse event
AR1: first order autoregressive structure
BSDI: Blepharospasm Disability Index
CDQ: Craniocervical Dystonia Questionnaire
CSRI: Client Service Receipt Inventory
CSQ: Client Satisfaction Questionnaire
EPR: electronic patient records
HADS: Hospital Anxiety Depression Scale
ICC: intraclass correlation coefficient
ICMJE: The International Committee of Medical Journal Editors
IPQ-R: Illness Perceptions Questionnaire Revised
JRS: Jankovic Rating Scale
MEH: Moorfields Eye Hospital
MLM: multilevel modelling
NHS: National Health Service
RCT: randomised controlled trial
REC: Research Ethics Committee
REML: Restricted Estimate Maximum Likelihood
R&D: Research and Development department
SAE: serious adverse event
UK: United Kingdom
VAS: visual analogue scale
